### Sample size calculations

The sample size calculation was performed using an estimated 120-day mortality rates of 8% and 1.7% in the control and intervention arms, respectively. These rates were extrapolated from the 90-day mortality rates of 1.7% (decompressing stoma (DS)) vs 7.2% (emergency resection (ER)) as well as the 3-year overall survival data in the propensity-score matched study by Veld, Tanis et al. [18]. The effect size was then reduced with an assumed 120-day mortality rate of 1.7% for the decompressing stoma group and 7% in the emergency resection group, resulting in a reduced effect size of 0.274 and an increased relative risk of 0.243.

To achieve the 80% power with a (two-sided) 5% significance level using a normal curve via arcsine transformation (Cohen, 1988, Chapter 6), at least 210 patients per arm (total 420 patients) need to be analyzed. To account for an expected 10% dropout rate, the target enrollment is 468 patients (234 per arm). Considering a 20% screen-failure rate, 588 patients will need to be assessed for eligibility. The power calculations were performed using SAS Version 9.4.

### Methods against bias

To address potential bias and ensure the integrity of the study, several methods have been implemented. As mentioned above, randomization and stratification will be used to allocate patients into the control and intervention groups. This process will be conducted using a secure online computer randomization system and will consider factors such as age, tumor stage, gender, ASA classification, presence of small bowel distention, and study center. By stratifying these variables, a balanced distribution can be achieved, reducing the risk of bias. To account for the delay between decompressing stoma placement and tumor resection in the intervention group, the primary endpoint of perioperative mortality has been adjusted to 120-day. This extension allows for a comprehensive evaluation of mortality rates in both groups with an appropriate timeframe.

The primary endpoint will be analyzed using the intention-to-treat (ITT) principle, and the final study report, in line with transparent reporting standards, will adhere to the CONSORT (Consolidated Standards of Reporting Trials) statement.

### Feasibility of the recruitment

Based on the estimated incidence of acute large bowel obstruction in Germany, it is anticipated that approximately 2500–5000 patients per year would be eligible for the study [4, 5]. In our own Department of Surgery, approx. 15–20 patients/year present with a left-sided obstructive colon cancer. We estimate that our center could include around 10 patients per year into the study. Based on these data and the retrospective Dutch trial by Veld, Tanis et al. [18], we estimate that a minimum of 35 large centers are needed to achieve the required sample size. Currently, 66 hospitals have committed to participate in the trial. The participating centers were selected according to recruitment potential, existing trial infrastructure and medical experience. To ensure adequate representation across different levels of care, basic care hospitals, and hospitals of the regular and priority care as well as maximum care hospitals such as university hospitals will be included in the recruitment.

### Oversight and monitoring

The study’s regulatory and supervisory functions are managed by the principal investigator (PI) in conjunction with the Coordination Centre for Clinical Trials (KKS) Dresden. The KKS Dresden assumes the data monitoring, which will follow a risk-based approach in line with the ICH-GCP (R2) guidelines. This includes assessing feasibility, availability and completeness of study material, ethics committee approvals, and providing adequate training to local staff. Monitoring activities will also verify written consent forms, source data, and accurate data entries. The frequency of monitoring will be determined based on the assessed risk to maintain data quality and study integrity. A patient advisory council board, comprised of individuals affiliated with the patient self-help organization ILCO, will offer invaluable support to the principal investigator (PI) and the coordinating center by contributing their personal expertise and experience when confronted with challenges that emerge throughout the course of the clinical trial. By implementing these methods, the study aims to minimize bias, ensure rigorous data collection and analysis, and provide a comprehensive and reliable evaluation of the chosen surgical approaches.

An independent data and safety monitoring board (DSMB), comprised of members without conflict of interest with the project and study investigators, will conduct regular interim analyses to assess the progress of the study and examine safety variables. The DSMB can terminate the study for safety reasons or due to early superiority, without predefined definitions.

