### Study design

The COMPASS trial is a multicenter, randomized, open-label study that will be conducted across 26 university hospitals and 40 academic hospitals in Germany. The trial was designed to show the superiority in regard to 120-day postoperative mortality among patients subjected to a two-stage bridge-to-surgery (BTS) procedure, as opposed to those undergoing a single-stage emergency resection (ER) for the management of obstructive left-sided colon cancer. Inclusion criteria involve patients presenting with symptoms of obstruction (abdominal distension, nausea, and/or vomiting) and having a left-sided colon tumor suspected of being colon cancer. Radiological assessments, including X-ray or a CT scan, must demonstrate a dilated colon with or without dilatation of the small intestine. Additionally, a high-grade suspicion of colon cancer should be identified on CT or endoscopy during the preoperative examination. Please refer to Fig. 1 for an illustration of the trial scheme.

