### Statistics

The statistical analysis plan for the study involves various tests and methods to analyze different endpoints. The chi-squared test will be applied to compare the perioperative 120-day mortality between the control and intervention arms using an intent-to-treat analysis. The significance levels were set to 5% (two-sided). The secondary endpoints will each be analyzed accordingly: The rate of primary anastomoses, permanent stomas, and 120-day complication rate will be investigated using the chi-square test. The 3-year overall survival will be examined using the Kaplan-Meyer estimator combined with the log-rank test. The treatment effect on the patient-reported quality of life will be analyzed using a regression analysis. Quality-adjusted survival will be analyzed using marginal models and non-parametric regression.

The statistical significance of stratification factors will be assessed. Propensity score matching may be used as a part of a supplementary analysis, to control for potential confounding factors that were not accounted for during sampling. In particular, a propensity score matching procedure with age as a continuous variable may be used to control for between-arm age differences. Statistical analyses of matched-sub-cohorts will have an exploratory character, providing additional information about effect sizes. The standardized mean differences and confidence intervals will be reported, and *p*-values will be provided as an additional information.

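### The DSMB may stop for early superiority with no predefined criterion while the final test keeps the full two-sided 5%, so type I error is not controlled at the stated level

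*Protocol article*

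**What the plan says.** Under Study design, the protocol article gives the aim: "The trial was designed to show the superiority in regard to 120-day postoperative mortality". Under Statistics, "The chi-squared test will be applied to compare the perioperative 120-day mortality between the control and intervention arms", by intention to treat, and "The significance levels were set to 5% (two-sided"). Sample size calculations uses the same level in a fixed-sample formula: "To achieve the 80% power with a (two-sided) 5% significance level using a normal curve via arcsine transformation". It takes "an assumed 120-day mortality rate of 1.7% for the decompressing stoma group and 7% in the emergency resection group" and arrives at 210 analysed patients per arm.

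Under Oversight and monitoring, an independent monitoring board "will conduct regular interim analyses to assess the progress of the study and examine safety variables". The next sentence is the stopping rule: "The DSMB can terminate the study for safety reasons or due to early superiority, without predefined definitions".

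The section Criteria for discontinuing the study covers the same ground differently. It mentions a board recommendation to end the trial only on grounds of participant safety. It also suspends the trial, pending board review, when severe morbidity or postoperative mortality is elevated in either arm. It gives no thresholds and does not mention superiority.

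**The concern.** A two-sided 5% level for a single final test holds only if that test is the one occasion on which superiority can be declared. Here superiority can also be declared earlier, at an unstated number of looks and by a criterion that the text says is not defined in advance. Neither the final level nor the sample size allows for this.

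The primary endpoint is death, so a safety review of mortality is also a look at the efficacy endpoint. The trial is open-label, so blinding offers no protection either.

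Three things are at stake:

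- The nominal level of the primary claim could not be stated after an early stop.
- A stop on few deaths tends to exaggerate the effect.
- Stopping recruitment early would leave fewer patients for the 3-year survival comparisons. The abstract's Discussion makes a change of practice conditional on the long-term oncological outcome not being compromised.

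**Working it through.** **Inputs.** From Sample size calculations: 7% and 1.7% mortality, two-sided 5%, 80% power, 210 analysed per arm, 10% dropout. From Statistics: chi-squared test at two-sided 5%. From Oversight and monitoring: repeated interim analyses, with superiority stopping allowed. Assumed, because not stated: 1 to 4 interims, equally spaced, plus the final test.

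**1. The plan's own figure.**
- h = 2·arcsin√0.07 − 2·arcsin√0.017 = 0.274, and relative risk = 0.017/0.07 = 0.243. Both match the article ("resulting in a reduced effect size of 0.274 and an increased relative risk of 0.243").
- n = 2·((1.960 + 0.842)/0.2740)² = 209.07, so 210 per arm; 210/0.9 = 233.3, so 234 per arm and 468 in total.

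The figure reproduces with the whole 5% spent on one test. Power by this formula at 210 per arm is 80.2%.

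**2. Overall type I error.** Under no difference, the statistic at look k of K behaves as Z_k = (X_1 + … + X_k)/√k with independent standard normal X. The overall error is the probability that any Z_k crosses its limit (10⁶ simulated trials):

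| Interims before the final test | p<0.001 at interims, 0.05 at final | p<0.05 at interims in favour of intervention only, two-sided 0.05 at final | two-sided p<0.05 at every look |
|---|---|---|---|
| 1 | 5.02% | 6.65% | 8.3% |
| 2 | 5.05% | 7.83% | 10.7% |
| 3 | 5.08% | 8.81% | 12.6% |
| 4 | 5.09% | 9.57% | 14.2% |

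For the last column, simulating deaths directly (210 per arm, uncorrected chi-squared, common mortality 4.35% to 7%) gives 7.7–8.1%, 10.4–10.5%, 11.8–12.3% and 13.1–14.3%.

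**3. How little data an early look holds.** Expected deaths are 210 × 0.07 = 14.7 and 210 × 0.017 = 3.6, about 18 in total and about 9 at halfway (105 per arm).
- 8 versus 1: pooled rate 9/210 = 0.0429, difference 7/105 = 0.0667, SE = √(0.0429 × 0.9571 × 2/105) = 0.0280, z = 2.39, p = 0.017.
- 7 versus 2: difference 5/105 = 0.0476, same SE, z = 1.70, p = 0.088.

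One death in the other arm decides the matter at an unadjusted 5%. A stop at 8 versus 1 would report a relative risk of 1/8 = 0.125, about half the 0.243 assumed in the design.

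**4. What a controlling boundary does at that look.** With one look at half information, Lan-DeMets O'Brien-Fleming spending gives p = 0.0031 at the interim and 0.0490 at the end. Haybittle-Peto (p<0.001, then 0.05) totals 0.0502. With 105 per arm, the first needs at least 9–0 or 11–1 deaths and the second at least 11–0 or 13–1. At the design rates the exact probabilities of crossing are about 9% and 3%.

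**The case against.** The interim analyses are described as looking at progress and safety, and no repeated formal efficacy test is set out. A reader might infer that the board will run a p<0.05 comparison at each look and that the error rate therefore exceeds 5%, reaching 8 to 14%. The documents do not support that as fact. They give no number of looks, timing or criterion. If the board required something like p<0.001, the inflation would be trivial. If early superiority means only lower mortality with the bridge-to-surgery approach, the 8 to 14% column does not apply. This part of the objection stands: the defect is loss of control, not a known excess.

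A reader might also infer that an early stop would leave the 3-year oncological question unanswered. That is not shown. The assessment table schedules visits to 36 months, and nothing says that follow-up of randomised patients would end. The 3-year comparison would be weakened by smaller numbers.

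Finally, boundaries are commonly left to an analysis plan or a board charter, and neither is at hand. That would answer a silent article, but this one says positively that no definitions are set in advance. A boundary held elsewhere would contradict that sentence, so it needs changing either way.

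**Conclusion.** The point holds as a matter of control. The article allows a superiority stop at repeated interim analyses with no predefined criterion, and it tests and sizes the trial as though there were one look. The stated 5% is not guaranteed.

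The true level cannot be calculated from the documents. Under the assumed 1 to 4 equally spaced interims it runs from about 5.0% to about 14%, depending almost entirely on a criterion that nobody is bound to. The sparse deaths at any early look make an informal judgement fragile. The two sections on stopping also differ on the grounds for ending the trial. This should be corrected before any comparative data are seen, because a rule added later would carry little weight.

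**What to change.** Replace the closing clause of the stopping sentence in Oversight and monitoring with one of two rules:

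- **(a)** No stopping for superiority; board reviews are for safety only.
- **(b)** A prespecified number and timing of efficacy looks, an alpha-controlling boundary, and the matching final level in Statistics. For example, one look when half the analysed patients have reached day 120, using Lan-DeMets O'Brien-Fleming (p about 0.003, final about 0.049) or Haybittle-Peto (p<0.001, final about 0.05). All other board reviews would then be safety-only.

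Then reconcile that section with Criteria for discontinuing the study, so that both give the same grounds for termination. The text should also say how a suspension for elevated mortality in one arm relates to the superiority rule, since the variable is the primary endpoint. Otherwise that route stays open whichever rule is chosen.

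**Cost.** Option (a) costs no power. For option (b), classical O'Brien-Fleming with one interim (final level about 0.048, slightly stricter than the example) gives 79.8% power at 210 per arm against 80.2%; about 211 per arm keeps 80%. A Pocock boundary would be dearer, at about 233 per arm. The other downside of (b) is that the interim would rarely stop the trial, with about a 9% or 3% chance at the design rates, which makes (a) a reasonable choice. Both need a protocol amendment and matching charter wording.

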### Data management

Personal health data will be recorded (Table 1) and archived by authorized study personnel for a minimum of 10 years, ensuring privacy by removing identifying information. Pseudonymized data will be transmitted to the Clinical Study Center for analysis and monitoring, accessible only to authorized personnel bound by confidentiality agreements. Participants have the right to revoke their consent for data storage and use, with the option for pseudonymized data to be retained unless specifically requested for complete deletion. Data entry is performed using a study software that complies with the requirements of applicable laws and guidelines, particularly ICH-GCP. The extent of database access and associated permissions are regulated through corresponding user roles. Data completeness, plausibility, and consistency are checked through programmed validations directly in the electronic case report form (eCRF) as well as supplementary manual checks outside of the eCRF. Any queries arising from these checks are sent directly to the respective study center within the eCRF. Corrections resulting from the responses to these queries are made by the study center in the eCRF.

**Table 1 Tab1:** Study assessment table

	**Baseline**	**Intervention**	**Follow-up**			
	**Visit 1/5**^a^	**Visit 2/6**^a^ (day of surgery)	**Visit 3/7**^**a**^ (POD 5 ± 1 days)	**Visit 4/8*** (day of discharge)	**Visit 9** (120 ± 7 days POD)	**Visits 10–12 (EOS)** (12, 24, and 36 months POD)
**Selection criteria informed consent**	•					
**Standardized imaging (radiography, CT)**	•				•	•
**Demographic data medical history ECOG status clinical-pathological features**	•					
**Laboratory tests**^b^	•		•			
**Serum CEA**	•				•	•
**Randomization**^c^	•					
**Study intervention**		•				
**Intraoperative results**		•				
**Postoperative results**			•	•	•	
**Quality of life**^d^	•				•	•
**Oncologic follow-up**					•	•

*CEA* carcinoembryonic antigen, *Ct* computed tomography, *EOS* end of study, *POD* postoperative day, *ECOG* Eastern Cooperative Oncology Group

^a^Intervention arm only

^b^Laboratory tests include: complete blood count, aspartate aminotransferase (AST; GOT), alanine aminotransferase (ALT; GPT), gamma-glutamyltransferase (γGT), lactate dehydrogenase (LDH), total bilirubin, creatinine, calculated glomerular filtration rate (GFR), albumin, and international normalized ratio (INR)

^c^Randomization must occur within 24 h after inclusion in the study at visit 1

^d^Quality of life will be assessed using the EORTC QLQ-C30 at visit 1/5* (baseline), visit 9 (POD 120), and visit 10–12 (12, 24, and 36 months after surgery)

### Criteria for discontinuing the study

The following termination rules or criteria are applicable:Individual patient termination: In the event that a patient, who has previously undergone a decompressive stoma procedure within the intervention group, becomes medically ineligible for the subsequent two-stage operation, their informed consent will be withdrawn.Exclusion of participating investigative centers: Investigative centers that deviate from the study protocol, primarily due to inadequate patient recruitment (less than one per year) and compromised data quality, will be excluded from the analysis.Study suspension: The entire study will be temporarily suspended following the occurrence of any of the subsequent events until evaluated by the data and safety monitoring board (DSMB):Elevated incidence of severe morbidity and/or postoperative mortality observed within either the intervention or control groupIncreased frequency of surgical interventions within either the intervention or control groupReceipt of a recommendation from the DSMB to prematurely terminate the study due to participant safety concerns in either of the two groups

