A recent retrospective propensity-score matched study by Veld, Tanis et al. demonstrated that the use of a decompressing stoma as part of the BTS approach resulted in a significantly decreased 90-day mortality rate compared to emergency resection (1.7% vs. 7.2%, *p* = 0.006) [18]. This difference was particularly pronounced in the patients over 70 years of age (3.5% vs. 13.7%, *p* = 0.027). Additionally, patients treated with a decompressing stoma underwent a higher proportion of minimally invasive resections (56.8% vs. 9.2%, *p* < 0.001) and had a greater incidence of primary anastomoses (88.5% vs. 40.7%, *p* < 0.001), a reduced occurrence of permanent stomas (23.4% vs. 42.4%, *p* < 0.001), and improved 3-year overall survival rates (79.4% vs. 73.3%, hazard ratio 0.36) [18].

These findings collectively suggest that the BTS approach for obstructive left-sided colon cancer has the potential to decrease perioperative mortality and improve quality of life by reducing the need for permanent stomas without compromising long-term oncological outcomes. However, it should be noted that the retrospective nature of the studies mentioned above precludes a comprehensive evaluation of dropout rates between decompressing stoma placement and subsequent resection. Thus, a prospective randomized trial is necessary to conduct an intention-to-treat analysis and validate these findings.

In this randomized multicenter trial, we aim to compare the outcomes of patients with obstructive left-sided colon cancer who undergo either emergency resection or the placement of a decompressing stoma as a bridge-to-surgery strategy.

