### Endpoints of the study

The study has identified several primary and secondary outcomes to evaluate the effectiveness and impact of the two surgical approaches for left-sided obstructive colon cancer. The primary outcome focuses on perioperative mortality within a 120-day period after surgery. Usually, perioperative death is defined as mortality within 90 days after surgery, but to compensate for the delay between decompressing stoma placement and tumor resection in the intervention group, we opted to extend the primary endpoint by 30 days according to recent studies [14, 18, 22].

Primary outcome:Perioperative 120-day mortality*Control group*: mortality within 120 days after emergency resection*Intervention group*: mortality within 120 days after decompressing stoma placement

Secondary outcomes:*Quality of life**Permanent Stoma rate**Stoma-associated complications**Quality-adjusted survival (QALY)**Number of resected lymph nodes**Number of R0 resections**3-year overall survival**3-year cancer-specific survival**3-year disease-free survival*

The secondary endpoints were developed in collaboration with experts as well as patient groups, such as the German ILCO, to ensure a comprehensive assessment of patient outcomes, including quality of life, complications, the rate of permanent stomas, and cancer-related factors.

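### Withdrawing stoma patients who become unfit for resection loses high-risk follow-up in the intervention arm only and undermines the intention-to-treat comparison of 120-day mortality

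*Protocol article*

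**What the plan says.** All references are to the protocol article.

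- **Criteria for discontinuing the study**, under termination for an individual patient: the rule concerns a patient "who has previously undergone a decompressive stoma procedure within the intervention group". If that patient "becomes medically ineligible for the subsequent two-stage operation, their informed consent will be withdrawn". There is no counterpart for the control group.
- **Endpoints of the study**: the primary outcome is "mortality within 120 days after decompressing stoma placement" in the intervention group and "mortality within 120 days after emergency resection" in the control group. The intervention-arm clock starts at the stoma and does not depend on a resection taking place.
- **Statistics**: the chi-squared test is to "compare the perioperative 120-day mortality between the control and intervention arms using an intent-to-treat analysis".
- **Methods against bias**: "The primary endpoint will be analyzed using the intention-to-treat (ITT) principle".
- **Introduction**: the retrospective design of earlier studies "precludes a comprehensive evaluation of dropout rates between decompressing stoma placement and subsequent resection". This is the stated reason for a randomised intention-to-treat trial.
- **Data management**: revoking consent is described as the participant's right, and pseudonymised data may be kept unless deletion is requested. Nothing is said about collecting further data afterwards.

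**The concern.** The rule ends participation on a post-randomisation, health-related event that can occur in one arm only. A patient judged unfit for resection at about the expected 30-day interval (Intervention group section) still has about 90 days at risk for the primary endpoint. Ending consent normally ends follow-up, so deaths in that period would go unrecorded. The control arm's sickest patients, by contrast, stay under observation to day 120.

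If unfit patients die more often than the rest, the loss makes the intervention arm look better than it is. A mortality benefit could then be declared because failures of the two-stage strategy were not counted. The patients lost are those between stoma and resection, the group the Introduction says the retrospective data could not account for. Permanent stoma rate and 3-year survival are exposed to the same selective loss. The rule also treats withdrawal of consent as something the protocol does to the patient.

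**Working it through.** **1. Reproduce the plan's sample size.** Inputs from Sample size calculations: an "assumed 120-day mortality rate of 1.7% for the decompressing stoma group and 7% in the emergency resection group", two-sided 5%, 80% power, arcsine method.

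- h = 2·asin(√0.07) − 2·asin(√0.017) = 0.274, as stated.
- n per arm = 2(1.960 + 0.842)²/h² = 209.07, so 210, as stated.
- With 10% dropout: 210/0.9 = 233.3, so 234 per arm and 468 in total, as stated.

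The sample size is not in dispute.

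**2. Expected deaths among 210 per arm.** Control: 210 × 0.07 = 14.7. Intervention: 210 × 0.017 = 3.6.

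**3. Assumptions.** The documents give neither the share w of the intervention arm that becomes unfit nor the 120-day mortality m in that share. Both are varied below. Every death among the unfit is taken to be unobserved.

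**4. What an observed 1.7% could hide.** With w = 5% and m = 30%, the unseen deaths number 210 × 0.05 × 0.30 = 3.15. If the remaining 95% die at 1.7%, the true rate in the whole arm is 0.95 × 0.017 + 0.05 × 0.30 = 0.031, or 3.1%.

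**5. False findings in favour of bridge-to-surgery.** Take true mortality as 7% in both arms, so there is no effect, with 210 randomised per arm. The unfit can be handled in two ways:

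- excluded: observed rate (0.07 − wm)/(1 − w) in 210(1 − w) patients, rounded;
- counted as alive: observed rate 0.07 − wm in 210 patients.

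The probability that the uncorrected chi-squared test is significant in favour of bridge-to-surgery was obtained by exact enumeration of the two binomial distributions. With complete follow-up it is 2.4% (nominal 2.5%).

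| Unfit share w | Mortality m | Rate if excluded | P, excluded | P, counted alive |
|---|---|---|---|---|
| 1% | 30% | 6.77% | 3.1% | 3.1% |
| 2% | 20% | 6.73% | 3.2% | 3.4% |
| 2% | 30% | 6.53% | 3.9% | 4.1% |
| 5% | 10% | 6.84% | 2.9% | 3.8% |
| 5% | 20% | 6.32% | 4.6% | 5.8% |
| 5% | 30% | 5.79% | 7.2% | 8.8% |
| 5% | 50% | 4.74% | 16.1% | 18.8% |
| 10% | 20% | 5.56% | 8.3% | 13.0% |
| 10% | 30% | 4.44% | 18.7% | 26.3% |

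If the unfit die at the same 7% as everyone else and are excluded, the figure stays at about 2.5%. Under exclusion, the inflation therefore comes from their excess risk and not from the smaller number analysed.

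**6. Does the dropout allowance help?** It adds 24 patients per arm, which replaces numbers. It does not correct a loss that is related to death and confined to one arm.

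**The case against.** The strongest reply is that removal from the analysis is inferred. The same section says that deviating centres are excluded from the analysis but does not say so for these patients. The article commits to intention to treat twice and allows earlier data to be kept after revocation. The odd wording about consent may be a loose way of saying that protocol treatment stops, and the full protocol or consent form may provide for vital status.

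Part of this stands. The article does not expressly drop these patients from the analysis set, so the defect is best described as missing day-120 status. That does not rescue the comparison. No section provides for follow-up after this withdrawal, and whether the patients are excluded or counted as alive, the result favours bridge-to-surgery when their mortality is above average. An analysis plan cannot recover outcomes that were never collected. If only the procedure was meant to stop, the sentence is wrong as worded, and sites will act on it.

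The second reply concerns size. The unfit share and its mortality are assumptions. Eligibility already excludes ASA IV or higher and life expectancy under 120 days, and deaths before a patient is declared unfit would still count. These points also stand. The 18.7% case places 3.0 of the arm's 7.0 percentage points of mortality (43%) among withdrawn patients. If half of the unfit in the 5%/30% case were followed after all, 205 patients would be analysed at (0.07 − 0.025 × 0.30)/0.975 = 6.41%, and 7.2% would fall to 4.3%. The effect on secondary endpoints has not been calculated.

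**Conclusion.** The rule is wrong as written and needs to be corrected. It contradicts the intention-to-treat commitments in Statistics and Methods against bias, and it works against the rationale in the Introduction. It applies to one arm, depends on health after randomisation, and takes effect while the primary endpoint is still open.

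The direction of the bias requires only that patients judged unfit for resection have higher 120-day mortality than the rest of their arm. Its size cannot be derived from the article. Over the assumed range, the chance of a false finding for bridge-to-surgery rises from 2.4% to about 3% under mild inputs, 7.2% at 5% unfit with 30% mortality, and 18.7% at 10% unfit with 30% mortality. These figures are for exclusion of the unfit and assume none of their deaths is observed. The planned sample size is unaffected.

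**What to change.** Reconcile Criteria for discontinuing the study with Statistics and Methods against bias by amendment:

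- Delete the automatic withdrawal of consent. Treat failure to proceed to resection, for any reason, as non-completion of the assigned strategy.
- State that such patients stay in the trial, are followed for vital status to day 120 and for the later endpoints to 36 months, and are analysed in the arm to which they were randomised.
- Record that resection was not performed, with the reason, as an outcome of the strategy.
- Reserve withdrawal of consent for the patient's own decision, and ask separately for permission to keep collecting vital status.

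The cost is a short protocol amendment and a line of consent wording. No extra patients are needed and no new visit is created. Patients who would have left under the present rule would attend the follow-up visits already in Table 1, which is some additional work for sites. The change takes no position on who is clinically fit for the second operation.
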